## 1.0 BACKGROUND AND RATIONALE

### 1.1 Management of severe acute malnutrition

Severe acute malnutrition (SAM) affects at least 19 million children worldwide, and through its detrimental effects on immune function, contributes to high child morbidity and mortality. Historically, the treatment of children with SAM included the systematic hospitalization of all cases and inpatient nutritional rehabilitation with milk-based diets over 3-4 weeks. In 2007, a joint United Nations statement endorsed a new model for the management of SAM that combines outpatient treatment with ready-to-use therapeutic foods (RUTF) for uncomplicated cases and inpatient treatment only for complicated cases. In this model, 80 to 90% of children with uncomplicated SAM are treated on a weekly outpatient basis, where they receive rapid health assessment and weight check by a nurse, a physical exam if signs of illness or weight loss are present, and a therapeutic ration of RUTF for home use. The shift from systematic inpatient to outpatient-based care has decreased the need for highly trained medical staff and inpatient bed capacity, reduced the risk of cross-infection among ill children, and importantly eliminated the burden on caregivers and children spending several weeks in hospital. Although outpatient care places increased responsibility on caregivers to supervise administration of RUTF at home and monitor the child's clinical condition between weekly visits, low mortality rates (e.g. 1 to 5 %) have been achieved.

While the outpatient treatment model represents great progress in the management of SAM, the current model remains impractical in some contexts, particularly in settings where geography (e.g. the south of Chad), security (e.g. Somalia) or nomadic livelihoods (e.g. Kenya) make frequent movements to a health facility difficult or impossible. In settings with a high incidence of acute malnutrition (e.g. Niger and Northeastern Nigeria), such frequent visits may also overwhelm public health capacity, resulting in reduced coverage of treatment. Therefore, in many settings, it may be necessary to identify an alternative delivery model for the outpatient management of uncomplicated SAM.

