### 3.7 Power calculations

Ten outpatient therapeutic feeding centers in this setting can be expected to admit total of 3,500 children for the treatment of uncomplicated SAM over 12 months (3,777 children admitted at 10 facilities in 2016). Assuming a baseline risk of nutritional recovery in the weekly

follow-up group of 0.80, intraclass correlation of 0.002 and significance level of 0.05 using the one-sided Score test, and allowing for 20% loss to follow up, a sample size of 350 children per health facility (2100 per group) will achieve 88% power to detect a non-inferiority margin difference between the group proportions of -0.05.

|                        | Difference in recovery between weekly vs. monthly follow up groups (n = 350 per site) |                  |                  |
|------------------------|---------------------------------------------------------------------------------------|------------------|------------------|
| Intraclass correlation | $\Delta = -0.15$                                                                      | $\Delta = -0.10$ | $\Delta = -0.05$ |
| 0.001                  | 1.00                                                                                  | 1.00             | 0.94             |
| 0.002                  | 1.00                                                                                  | 1.00             | 0.88             |
| 0.01                   | 1.00                                                                                  | 0.97             | 0.54             |

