### 3.9 Statistical analysis

The primary outcome is nutritional recovery. Secondary outcomes include hospitalization, average daily weight gain among recovered children, defaulting, and relapse within 3 months.

All analyses will use the intention-to-treat principle and account for the stratified cluster design. We will use generalized estimating equations and robust standard errors to compare the proportion of children recovered, hospitalized, defaulted or relapsed within 3 months, and mixed effects models to compare average daily weight gain.

Interim analysis at 6 months of inclusion will be conducted to ensure the safety of children included. No adjustment will be made for multiple testing. All P values will be 2-sided, with  $P < 0.05$  considered statistically significant. Analyses will be performed using SAS version 9.3 or higher (SAS Institute Inc., Cary, NC).

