#### 4.9 Post-discharge follow-up

All children will receive a home visit by a community health worker 3 months following discharge from the nutritional program, regardless of type of discharge (e.g. recovered, default or non-recovered), requesting the caregiver and child to return to the outpatient therapeutic center. At each post-discharge visit, anthropometric measures (e.g. weight, height and MUAC) will be taken; history of nutritional treatment within the last 3 months will be assessed by maternal report; and caregivers knowledge, attitudes and practices related to the key danger signs and MUAC assessment will be assessed by standardized questionnaire (see Annex 9.2). Compensation (e.g. 2 pieces of soap) for participation in the post-discharge visit will be provided to caregivers at the end of the visit.

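### The 88% power is computed with no loss removed and does not say whose recovery rate 0.80 is; at the expected intake, power under the planned intention-to-treat comparison could be as low as about 76%

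*Protocol*

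**What the plan says.** Section 3.7 (Power calculations) gives the weekly-group assumption as "follow-up group of 0.80, intraclass correlation of 0.002 and significance level of 0.05 using the one-sided Score test". The same sentence continues "allowing for 20% loss to follow up, a sample size of 350 children per health facility", gives 2,100 per group in brackets, and claims 88% power for a non-inferiority margin of -0.05. The table under it, headed 350 per site, gives 0.94, 0.88 and 0.54 for that margin at intraclass correlations (ICCs) of 0.001, 0.002 and 0.01. Expected intake is 3,500 children at ten centers over 12 months, against 3,777 admitted in 2016.

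Section 3.9 (Statistical analysis) says "All analyses will use the intention-to-treat principle and account for the stratified cluster design" and names the proportion recovered as a compared quantity, with the proportion defaulted compared separately. Section 4.9 (Post-discharge follow-up) schedules a home visit "regardless of type of discharge (e.g. recovered, default or non-recovered", so default is recorded as a way of leaving the program distinct from recovery. Section 4.8 makes a child a defaulter after three consecutive missed visits in the weekly group or one in the monthly group.

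**The concern.** A loss allowance normally means that lost children drop out of the analysed set and enrolment is raised to compensate. The assumed rate is then a rate among children with a known outcome. An intention-to-treat comparison of the proportion recovered normally keeps every enrolled child in the denominator. A child who stops attending would typically be recorded as a default, and so most naturally as not recovered. Under that analysis, loss lowers the event rate and raises the binomial variance; it does not simply reduce the number analysed. Section 3.7 does not say which of these its 0.80 belongs to.

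What is at stake is the chance that a monthly schedule with truly equal recovery fails to show non-inferiority. The plan puts that at 12%. On the least favourable reading at the expected intake it is about 24%.

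**Working it through.** **Inputs.** From section 3.7: recovery p = 0.80, ICC = 0.002, one-sided alpha 0.05 with a score test, margin 0.05, 20% loss, 350 per facility, 2,100 per group. From section 3.1: ten centers randomized 1:1, so five per group. Assumed here: equal true recovery in both groups, equal center sizes, and a normal approximation.

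**Formula.** With m children analysed per center, SE = sqrt(2p(1-p)[1 + (m-1)ICC] / (5m)) and power = Phi(0.05/SE - 1.645). The Farrington-Manning score version agrees to within 0.3 percentage points and is used in the table below.

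**Reproducing the plan's figure.** Take p = 0.80 and m = 350.
- Design effect: 1 + 349 x 0.002 = 1.698.
- Effective number per group: 1,750 / 1.698 = 1,031.
- SE = sqrt(0.32 / 1,031) = 0.0176.
- Power = Phi(2.84 - 1.645) = 0.88.

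At ICC 0.001 and 0.01 the same steps give 0.94 and 0.54. All three match the printed row, so that row is for 350 children analysed per center with nothing removed for loss.

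**The number enrolled.** 5 x 350 = 1,750 per group, and 1,750 x 1.2 = 2,100 = 5 x 420. The 2,100 therefore looks like 1,750 raised by 20%. Two groups of 2,100 make 4,200 children, above both the 3,500 expected and the 3,777 admitted in 2016. The expected intake gives 350 enrolled per center.

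**The readings of 0.80** (ICC 0.002, margin -0.05):

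| Meaning of 0.80 and handling of loss | 350 enrolled per center | 420 enrolled per center (2,100 per group) |
|---|---|---|
| All enrolled; all analysed | 88.3% | 91.0% |
| Retained only; lost children excluded (280 or 336 analysed) | 84.2% | 87.6% |
| Retained only; lost children kept, none recovered (p = 0.80 x 0.80 = 0.64) | 76.5% | 80.1% |

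In the last row p(1-p) rises from 0.160 to 0.230, an increase of 44%. At 350 per center, SE = sqrt(0.4608 / 1,031) = 0.0211 and power = Phi(2.36 - 1.645) = 0.76.

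**If some lost children count as recovered.** If a fraction r of them do, overall recovery is 0.64 + 0.20r.

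| r | Overall recovery | 350 per center | 420 per center |
|---|---|---|---|
| 0.2 | 0.68 | 78.5% | 82.1% |
| 0.4 | 0.72 | 81.1% | 84.5% |
| 0.6 | 0.76 | 84.4% | 87.5% |

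**Other ICCs.** At p = 0.64 and 350 per center, power is 84% at ICC 0.001 (printed 0.94) and 42% at ICC 0.01 (printed 0.54).

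**The case against.** A reader might infer that 80% recovery and 20% loss contradict each other, since with the background statement that "low mortality rates (e.g. 1 to 5 %) have been achieved" the shares total 101 to 105%. The documents do not support that. The sum mixes an expected rate, a planning allowance and a mortality range quoted for outpatient care in general; these are not a partition of this trial's outcomes. The two figures coexist without difficulty if 0.80 is a rate among retained children. If 0.80 covers all enrolled children and 20% really are lost and not recovered, every retained child would have to recover, which is implausible but not impossible.

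A reader might also infer that the true power is 76%. That needs lost children to be counted as not recovered, which the protocol nowhere states. Section 3.9 gives no rule for unknown outcomes, and such a rule may properly sit in a statistical analysis plan. Section 4.9 lists discharge types to say who gets a home visit; it does not define the primary analysis. Loss to follow-up is never equated with default, and section 4.8 plans home tracing so that data are complete. The wording "follow-up group of 0.80, intraclass correlation of 0.002" can be read as the whole weekly group, and on that reading 88% is not overstated.

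These objections rule out both stronger readings. They do not rescue the power statement as written. At the expected intake, 88% requires 0.80 to be the all-enrolled rate, and then the statement that 20% loss has been allowed for does no work. Tracing under section 4.8 is described as establishing vital status and the reason for absence and asking the caregiver to return. It would not by itself show that a child met the recovery criteria.

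**Conclusion.** The point holds as a conditional one. The printed powers are correct for the inputs that produce them, but those inputs contain no loss, and the denominator of 0.80 is not given. At 350 enrolled per center, power for the -0.05 margin at ICC 0.002 is 88% if 0.80 covers all enrolled children, 84% if it covers retained children and the lost are excluded, and as low as 76% if the lost are kept as not recovered. At 2,100 per group the last two figures become 88% and 80%, but that number exceeds the expected admissions. The possible shortfall at the expected intake is therefore 0 to 12 percentage points. The 12-point end rests on 20% actual loss with none of those children counted as recovered. All figures assume equal true recovery in the two groups and the protocol's own ICC and one-sided 5% level. The difference between 1,750 and 2,100 per group is a separate inconsistency, and correcting it alone would not settle this one.

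**What to change.** In section 3.7, state whether 0.80 is recovery among all enrolled children or among those retained, so that it matches the intention-to-treat proportion in section 3.9.

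- If it is the all-enrolled rate, delete the 20% loss allowance and keep 88% at 350 per center.
- If it is a retained-children rate, restate the control recovery rate on the all-enrolled basis: 0.64 if no lost child is counted as recovered, or a justified value above that. Then recompute the power statement and every row of the table on the number actually expected to enrol, and accept the less favourable figure.

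The cost is a reworded paragraph and a recomputed table. No added enrolment and no change to trial conduct is required.

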### 3.0 METHODOLOGY

#### 3.1 Study design

This study will be conducted as a stratified cluster randomized trial of a monthly schedule of follow up in the treatment of uncomplicated SAM among children aged 6 to 59 months. The unit of randomization will be the outpatient therapeutic feeding center. The 10 health centers supported by UNICEF will be stratified by size ( $\pm 500$  admissions per site), and centers within a stratum will be randomized in a 1:1 ratio to one of two schedules of treatment: (1) standard weekly visits or (2) monthly visits with support for home-based surveillance.

Distribution of the therapeutic feeding rations, as well as medical and anthropometric surveillance, will take place on a weekly or monthly basis until discharge according to the random assignment of the site. Caregivers in the monthly visit group will receive additional instruction at admission regarding home-based MUAC measurement and clinical surveillance.

Regardless of intervention assignment, all children with uncomplicated SAM will receive standard medical care on admission as per national guidelines, and a home visit 3 months following discharge from the nutritional program. Additional data collection, including coverage assessment and economic costing analysis will be used to address the secondary objectives related to the evaluation of coverage and cost-effectiveness, respectively.

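### Section 3.7 equates 350 children per facility with 2,100 per group, but five facilities per arm give 1,750; the 88% power matches 350 analysed per site, which the expected intake does not leave after 20% loss

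*Protocol*

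**What the plan says.** Protocol Section 3.7 starts from intake: "Ten outpatient therapeutic feeding centers in this setting can be expected to admit total of 3,500 children" over 12 months, and it notes 3,777 admissions at ten facilities in 2016. It assumes recovery in the weekly "follow-up group of 0.80, intraclass correlation of 0.002", a "significance level of 0.05 using the one-sided Score test", and a "non-inferiority margin difference between the group proportions of -0.05". It then states the result: "allowing for 20% loss to follow up, a sample size of 350 children per health facility (2100 per group) will achieve 88% power". The table below that sentence is headed with 350 per site. For the -0.05 column it prints 0.94, 0.88 and 0.54 at intraclass correlations of 0.001, 0.002 and 0.01.

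Section 3.1 names ten health centers as the units of randomization and says that "centers within a stratum will be randomized in a 1:1 ratio to one of two schedules of treatment". Section 3.6 repeats the 1:1 ratio. Section 4.2 sets recruitment at 12 months or more, and the timeline in Section 4.11 runs enrolment from March 2018 to February 2019.

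**The concern.** One sentence gives a per-facility number, a per-group number, a loss allowance and a power, and these do not fit together. Five facilities of 350 do not make 2,100. The per-facility figure of 350 also equals the expected admissions per center, which is a count before any loss, yet the power attached to it is what 350 analysed children would give.

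Two things are at stake. The first is the power for the primary non-inferiority comparison that ethics committees and readers are told to expect. The second is the enrolment target: 350 and 420 per site differ by 70 x 10 = 700 children over the trial, and a reader cannot tell which applies.

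**Working it through.** **Inputs.** Recovery 0.80 in the weekly group, intraclass correlation (ICC) 0.001, 0.002 or 0.01, one-sided alpha 0.05 with the score test, margin -0.05, loss 20%, and 350 per facility (all Section 3.7). Ten centers at 1:1, so k = 5 per arm (Sections 3.1 and 3.6). Two assumptions are mine: true recovery is 0.80 in the monthly group as well, the usual non-inferiority alternative, and the table's column values are margins.

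**Head count.**
- 5 x 350 = 1,750 per group; 10 x 350 = 3,500 in total.
- 2,100 / 5 = 420 per facility; 2 x 2,100 = 4,200 in total.
- 2,100 is also 6 x 350 and 1,750 x 1.2.

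**Formula.** With m analysed per site, the design effect is DE = 1 + (m - 1) x ICC and the effective size per arm is n = 5m / DE. At a margin of -0.05 the restricted estimates under the null are 0.7727 and 0.8227. Then

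s0 = sqrt[(0.7727 x 0.2273 + 0.8227 x 0.1773) / n], s1 = sqrt[(2 x 0.80 x 0.20) / n],

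power = Phi[(0.05 - 1.645 x s0) / s1].

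**Reproducing the stated 88%** (m = 350, ICC 0.002): DE = 1 + 349 x 0.002 = 1.698; n = 1,750 / 1.698 = 1,031; s0 = 0.01766; s1 = 0.01762; power = 0.883.

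**With 20% loss from 350 enrolled** (m = 350 x 0.8 = 280): DE = 1.558; n = 1,400 / 1.558 = 899; s0 = 0.01892; s1 = 0.01887; power = 0.842.

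**All configurations, margin -0.05:**

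| Analysed per arm | ICC 0.001 | ICC 0.002 | ICC 0.01 |
|---|---|---|---|
| Protocol table | 0.94 | 0.88 | 0.54 |
| 5 x 350 | 0.938 | 0.883 | 0.538 |
| 5 x 280 (350 enrolled, 20% lost) | 0.899 | 0.842 | 0.520 |
| 5 x 336 (420 enrolled, 20% lost) | 0.931 | 0.876 | 0.535 |
| 5 x 420 | 0.960 | 0.910 | 0.551 |
| 6 x 350 | 0.967 | 0.928 | 0.604 |
| 6 x 280 | 0.940 | 0.895 | 0.584 |

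At the -0.10 margin with ICC 0.01, 5 x 350 gives 0.966 against the printed 0.97; the other five cells are 1.00. Of the configurations tried, only 5 x 350 matches all nine cells. The 5 x 336 row comes close and misses one cell (0.93 against 0.94 at ICC 0.001).

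**The enrolled-420 reading.** Inflating 1,750 for 20% loss is 1,750 / 0.8 = 2,188, not 1,750 x 1.2 = 2,100; 420 enrolled leaves 336, not 350. Exactly 88% needs about 344 analysed, or 344 / 0.8 = 430 enrolled per site. Recruiting 4,200 children takes 4,200 / 3,500 x 12 = 14.4 months at the expected intake, or 4,200 / 3,777 x 12 = 13.3 months at the 2016 rate.

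**The case against.** The strongest reply is that 350 is the number analysed and 2,100 the number enrolled, since 2,100 = 1,750 x 1.2. The loss would then be allowed for, if slightly short, and 87.6% rounds to the stated 88%. This has weight. A reader might infer from the reproduced table that the 88% simply ignores the 20% loss; the protocol does not support putting it so flatly, because it never says whether 350 is enrolled or analysed. Against the reply, the sentence offers 350 per facility and 2,100 per group as one and the same sample size, and 350 is the expected admissions per center. Even on this reading the text needs correcting, and the 4,200 children do not fit the enrolment dates in Section 4.11 at either intake rate.

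A reader might also infer that the sites cannot supply the trial. That goes too far. Section 4.2 allows recruitment beyond 12 months. At the 2016 intake, about 378 enrolled and 302 analysed per site would give about 86%. Nor is enrolment open-ended, since it is bounded by calendar dates; only the target number is ambiguous.

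The 84% assumes that every lost child leaves the analysis. Section 3.9 specifies intention to treat, and if defaulters are kept as not recovered, the analysed number falls less. The 84% is therefore a scenario.

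Finally, 2,100 could be left over from a design with six sites per arm. Nothing in the protocol shows twelve sites, and 6 x 350 and 6 x 280 do not fit the table. Whether ten clusters call for a small-sample correction is a separate question, commonly left to the analysis plan; this point does not depend on it.

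**Conclusion.** The contradiction between 350 per facility and 2,100 per group is certain and needs no assumption beyond five centers per arm. The power statement is wrong or incomplete on either reading:

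- **350 enrolled:** power after 20% loss is about 84% at ICC 0.002, 90% at 0.001 and 52% at 0.01, against the printed 88%, 94% and 54%.
- **420 enrolled:** power is about 87.6% at ICC 0.002, the inflation is short of 2,188 per group, and the children needed exceed the intake expected in the planned 12 months.

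The wording and the intake figure favour the first reading but do not prove it. These figures assume equal recovery of 0.80 in both groups, equal cluster sizes, and lost children out of the analysis. The effect is about 4 points at the base ICC and 84% remains above 80%. This should be fixed; it does not put the design, margin or analysis in doubt.

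**What to change.** Restate Section 3.7 with one set of numbers, enrolled and analysed, per site, per group and in total, and make the power and the table match it. The sponsor must say which set is meant.

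- **If the planned 12-month intake governs:** 350 enrolled per site, 1,750 per group, 3,500 in total, 280 analysed per site after 20% loss, power about 84% at ICC 0.002. Regenerate the table at 280 analysed per site and remove the figure of 2,100.
- **If 420 per site is meant:** say that it is the enrolled number, give 336 analysed per site and about 87.6% power, regenerate the table at 336, and reconcile the 4,200 children with the expected intake and the enrolment dates in Section 4.11.

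In either case, state whether children lost to follow-up leave the primary analysis or count as not recovered, because the analysed number depends on it.

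The cost is a corrected paragraph and a recalculated table. The first option needs no extra children but reports a lower power. The second needs about 1.3 to 2.4 months of recruitment beyond the planned 12.

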### 3.8 Data entry, management and quality control

All of the information required by the study protocol will be entered on standardized case report forms (CRF) provided by the principal investigator (provided in Annex 9.2). The study nurses assigned to each health center and Field Investigator will validate all CRFs for completeness and accuracy, signing and dating each to attest to his/her responsibility for the quality of all data recorded and that the data represents a complete and accurate record of each child's participation in the study. All validated CRFs will be double-entered in an electronic database, compared and verified for accuracy. Data quality will be enforced through a variety of mechanisms, including referential data rules, valid values, range checks, and consistency checks against data already stored in the database (i.e., longitudinal checks).

A data validation plan will be prepared by the Principal Investigator. Errors will be detected by programs designed to detect missing data or specific errors in the data. These errors will be summarized along with detailed descriptions of the specific problem in a Data Query Report, which will be sent to the Field Investigator for resolution by checking the original forms for inconsistency, checking other sources to determine the correction, and modifying the original (paper) form as appropriate. Written documentation of changes will be available via electronic logs. A complete back up of the study database will be performed twice a month; incremental data back-ups will be performed on a daily basis. The data manager will provide monthly email reports with information on missing data, missing forms, and missing visits to the sponsor. Epicentre alone will have full access to the data.

